## 1083 5.2.4 Structural and process measures

1084 The implementation strategies evaluated by this study represent a complex intervention involving  
1085 multiple interacting components (41). As such, measures of infrastructure and processes for care are  
1086 needed to assess fidelity of implementation, clarify causal mechanisms and identify influential  
1087 contextual factors to inform further refinement, adaptation and tailoring to different settings.

1088

### 1089 5.2.4.1 Centre-level structural measures

1090 Centre staffing, equipment and access to specialist services, including staff turnover as a variable  
1091 that may influence the sustainability of implementation.

1092

### 1093 5.2.4.2 Centre-level process measures

1094 Staff training (via QStream and other initiatives), implementation of and adherence to the guidelines  
1095 and documentation quality. Discussion of pain and other symptoms and their management at  
1096 multidisciplinary team meetings/case reviews will be tracked.

1097

### 1098 5.2.4.3 Staff-level process measures

1099 Time spent in training and on cancer pain screening, assessment and management by clinical staff  
1100 and front desk administrative staff. Staff will be invited to complete an anonymous online survey  
1101 via the Survey Monkey platform that asks them their role at the centre and three separate questions  
1102 on how much time they spent on cancer pain screening, assessment and management during their  
1103 last complete work day (Appendix 5).

1104

### 1105 5.2.4.4 Patient-level process measures

1106 Number and duration of consultations, multi-disciplinary input, primary care support, and standards  
1107 of care recommended by the guidelines. Items of particular interest will be instances of screening,  
1108 assessment, patient education, regular analgesia (agent, route, dose), breakthrough analgesia (agent,  
1109 route, dose, and number of times taken) and management of side-effects (preventative and  
1110 treatment), as well as any other anti-cancer, interventional and non-pharmacological methods used  
1111 to address pain. The clinical audit tool (administered by research assistants to standardise between  
1112 conditions/centres), will assess participants' clinical records retrospectively. Because it is often not  
1113 documented in medical records, patients' receipt (or otherwise) of pain education will be measured  
1114 by asking the patient at each time-point for telephone follow-up.

1001/ 4th September, 2018

1115 **5.2.5 Descriptive/control variables**

1116  
1117 **5.2.5.1 Patients**

1118 **5.2.1.1.1 Demographics**

- 1119 1. Age  
1120 2. Gender  
1121 3. Availability of an unpaid carer:  
1122 a. lives with carer  
1123 b. lives alone but carer available  
1124 c. lives with non-carer  
1125 d. lives alone, no carer  
1126 4. Postcode  
1127 5. Country of birth  
1128 6. Language spoken at home  
1129 7. Aboriginal and/or Torres Strait Islander status

1130 **5.2.1.1.2 Cancer diagnoses**

1131 The following clinical data will be collected:

- 1132  
1133 i. Site  
1134 ii. Tumour stage  
1135 iii. Sites of metastases  
1136 iv. Time since diagnosis  
1137 v. Current treatment

1138 **5.2.1.1.3 Comorbidities**

1139 Comorbidities will be identified that influence pain or its management according to the guidelines.  
1140 Conditions of interest will include painful conditions (e.g. arthritis), renal impairment, gastro-  
1141 intestinal ulcers and conditions causing cognitive impairment (e.g. dementia).

1142 **5.2.1.1.4 Performance status**

1143 Performance status will be measured using whatever tool is routinely in practice at each site. It is  
1144 anticipated that these will most often be the Karnofsky Performance Status (KPS) (54) or Australia  
1145 - modified Karnofsky Performance Status (AKPS) (55) at palliative care sites and the Eastern  
1146 Oncology Cooperative Group (ECOG) Performance Status (56) at oncology sites. Conversion  
1147 between these scales to enable comparability will be undertaken via validated methods where  
1148 available (57).

1150 **5.2.1.2 Carers**

- 1151 1. Age  
1152 2. Gender  
1153 3. Relationship to patient (child, parent, partner, other)  
1154 4. Lives/does not live in the same household as the patient  
1155 5. Country of birth  
1156 6. Language spoken at home  
1157 7. Aboriginal / Torres Strait Islander status  
1158

1159 **5.2.1.3 Centre staff**

1160 Role (front desk administrative, medical, nursing, allied health).

I001/ 4th September, 2018

### **5.3 Qualitative sub-study**

Patients and carers (n=20 respectively) who participate will be invited to give informed consent to take part in a qualitative sub-study. Interviews will focus on experience and usefulness of symptom assessment and management, the patient-held resources and degree of person-centredness and coordination of care using a focussed question route. See Appendix 8 for an interview guide.

Health professionals who give informed consent will participate in staff focus groups or interviews at each centre which will explore perceptions of what has worked well regarding the implementation strategies and potential improvements. See Appendix 9 for a focus group/interview guide.

### **5.4 SAFETY MONITORING**

#### **5.4.1 Reporting of incidents**

Clinical staff and managers at participating centres will be encouraged to report to the project team any adverse incidents that they believe may be related to the project intervention or study procedures. See Appendix 10 for the template.

##### **5.4.1.1 Follow-up of incidents**

After the initial report, investigators are required to follow-up each incident and provide further information both to the coordinating centre (ImPaCCT office, UTS) and the approving HREC if required. All incidents reported as ongoing are to be reviewed at subsequent visits or appointments in order to report progress and resolution.

All events are to be followed until:

- resolution;
- the event can be explained;
- a participant involved is lost to follow-up;
- a participant involved dies.

Reports are to contain details of follow-up investigations, result reports or reports from other consultations, and are to be updated in a report to the coordinating centre and the approving HREC.

#### **5.4.2 Stopping rules**

The study will be stopped if or if reporting of incidents indicate that review of the study protocol is required or if new literature indicates findings that answer the research questions.

#### **5.4.3 Monitoring**

Reports of incidents will be sent to the Trial Management Committee and the approving Hospital Ethics Review Committee within two weeks of knowledge of the event.

##### **8.1.1.1 The Trial Management Committee**

Each meeting of the Trial Management Committee will receive from the coordinating centre a summary report of the incidents reported by the investigators. This summary report will be reviewed for reporting compliance, trends in incidents, and outstanding incidents that require specific attention. All Trial Management Committee discussions will be minuted, with actions detailed, and reviewed at the subsequent meeting.

1205 8.1.1.2 Hospital Ethics Review Committees  
1206 Incidents that meet the requirements to reported to the approving HREC will be reported in the  
1207 required format and timeframe stipulated by each individual committee.  
1208

## 1209 **5.5 STATISTICS**

### 1210 **5.5.1 Statistical analysis**

1211 For the main analysis, linear mixed models (5) will be used to model the outcomes of interest, while  
1212 accounting for the clustering and longitudinal design. Although designed for the analysis of  
1213 continuous outcomes, we have conducted computer simulations to confirm that this approach will  
1214 work very well for the pain and other NRS scores that are measured on a ten point scale. The linear  
1215 mixed modeling framework is very flexible. For example, it will allow for testing whether treatment  
1216 effects diminish over time. It will also allow the incorporate of additional covariates of interest, for  
1217 instance patient age, gender, ethnicity and other factors related to their type of disease; and  
1218 inclusion of covariates that reflect characteristics of the study centres. Statistical analysis will be  
1219 performed using the library lme4 in the R package (58). Analyses will be repeated for all patients  
1220 and patients newly referred during the intervention arm to control for the possibility that outcomes  
1221 are influenced by care received prior to the intervention being implemented. For secondary patient  
1222 outcomes, analyses will be repeated for patients with clinically significant ( $\geq 2$ ) and moderate-severe  
1223 ( $\geq 5$ ) worst and average pain.

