## **Analysis**

163 For the main analysis, linear mixed models (5) will be used to model the outcomes of interest, while  
164 accounting for the clustering and longitudinal design. Sensitivity analyses will be used to explore  
165 the effects of the intervention for different sub-groups and to explore objective 3.  
166 The primary outcome for cost-effectiveness analysis will be the incremental cost per additional  
167 responder at the end of Week 1 (response is defined as a clinically important improvement of 30%  
168 on a 0-10 NRS 1 week post-screening for those with moderate-severe ( $\geq 5$ ) worst pain). Quality of  
169 life data collected at weeks 1, 2 and 4 will be used to conduct a modelled cost-utility analysis. As  
170 economic data may be skewed, confidence intervals will be estimated with bootstrap methods (6).  
171 Sensitivity analysis will examine the effect of assumptions and determine which cost components  
172 drive the results.  
173  
174 Thematic coding and classifying techniques will underpin the analysis of semi-structured interviews  
175 and focus groups (7).  
176  
177  
178

|     |                                                                                                                         |           |
|-----|-------------------------------------------------------------------------------------------------------------------------|-----------|
| 179 | CONTENTS                                                                                                         |           |
| 180 | TRIAL SUMMARY .....                                                                                              | 5  |
| 181 | CONTENTS .....                                                                                                   | 9  |
| 182 | LIST OF ABBREVIATIONS .....                                                                                      | 11 |
| 183 | BACKGROUND AND RATIONALE .....                                                                                   | 12 |
| 184 | 1.1 REVIEW OF THE LITERATURE.....                                                                                       | 12        |
| 185 | 1.2 WORK BY THE CURRENT TEAM.....                                                                                       | 13        |

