### 5.2.1 Primary outcome

The primary outcome will be the probability that patients screened as having moderate-severe ( $\geq 5$ ) worst pain will experience a clinically important improvement 1 week later, as measured by 30% on a 0-10 numerical rating scale (NRS).

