### 1224 **5.5.2 Sample size and power calculations**

1225 To assess the appropriate study sample size and compute study power, we used a carefully designed  
1226 computer simulation allowing for 20% dropout by both sites and patients. Drawing on data from  
1227 1,612 consecutive patients (59), outcome data were generated to mimic pain scores we expect to see  
1228 in the presenting population. We generated data from a beta distribution (scaled 0 to 1), rescaled to  
1229 lie between 0 and 10, then rounded to integer values. We then discarded patients with scores of  $< 2$   
1230 to represent the sample of interest. We allowed centre-specific means to vary between .05 and .15 to  
1231 generate an appropriate intra-class correlation. We used a standard minimally important difference  
1232 of .5 effect size (60). To more closely represent reality, we allowed for variation in the responses of  
1233 each patient to intervention. Once a hypothetical study population had been generated, we ran a  
1234 linear mixed model that included an intervention effect as well as an intervention by time effect, as  
1235 well as a random centre effect. We repeated this whole process several hundred times and then  
1236 estimated power by computing the proportion of times that the null hypothesis would be rejected.  
1237 We did this both for the main intervention effect, as well as the intervention by time effect. Two-  
1238 sided hypothesis tests with type I errors of 0.05 were used. Assuming 82 patients per centre at 6  
1239 sites ( $N=492$ ), our study will have  $>90\%$  power to detect the main effect. The study will oversample  
1240 by 2 sites (i.e. a total of 8 sites) and 18 patients per site (i.e.  $N=100$  at each site) to allow for drop-  
1241 out.

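### The primary outcome is a yes/no 30% response, but the only main analysis stated is a linear mixed model defended for 0-10 pain scores; a model for response should be named

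*Protocol*

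**What the plan says.** Section 5.2.1 begins "The primary outcome will be the probability that patients screened as having moderate-severe" worst pain (5 or more) "will experience a clinically important improvement 1 week later, as measured by 30% on a 0-10 numerical rating scale". Each patient therefore either responds or does not, and the primary objective (trial summary and 2.2.1) is worded the same way.

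For the analysis, 5.5.1 says: "For the main analysis, linear mixed models (5) will be used to model the outcomes of interest, while" allowing for clustering and the longitudinal design. The Analysis paragraph of the trial summary repeats it: "linear mixed models (5) will be used to model the outcomes of interest, while". Section 5.5.1 acknowledges that the method was designed for continuous outcomes and answers this with simulations that it will "work very well for the pain and other NRS scores that are measured on a ten point scale". Neither place names a model, link function or effect measure for a binary response.

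Two other sections bear on how the primary outcome is understood:

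- 5.5.2 (power) generates pain scores scaled to "lie between 0 and 10, then rounded to integer values", discards patients scoring below 2, applies a 0.5 effect size and fits a linear mixed model with intervention, intervention-by-time and random centre effects. No response rate appears.
- 5.2.3.1, item 2, sets the minimally important difference at 0.5 SD and says this is the same as for the primary outcome. Item 1 of that section lists mean reduction in worst pain at one week, in patients scoring 2 or more and 5 or more, as a secondary outcome.

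**The concern.** The analysis section does not settle what will be modelled for the primary endpoint. Two competent analysts could follow 5.5.1 and report different primary results: one a difference in mean pain score, the other a difference in the proportion responding. The stated justification, the power simulation and 5.2.3.1 all lean towards the first. That would make the main analysis a test of a secondary outcome.

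The primary objective asks about the probability of response, and the primary economic result in 5.5.3 is cost per additional responder. Both need an effect on response. A mean-score difference supplies neither. Leaving the choice open also leaves discretion over the primary test.

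**Working it through.** **1. The passages side by side**

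| Place in the protocol | How the primary outcome is treated |
|---|---|
| Trial summary, 2.2.1, 5.2.1 | Response yes/no, screening score 5 or more |
| 5.5.1 and trial summary, Analysis | Linear mixed model, defended for NRS scores |
| 5.5.2 | Mean 0-10 score, patients scoring 2 or more, 0.5 effect size |
| 5.2.3.1, item 2 | 0.5 SD difference |
| 5.5.3 | Responders |

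**2. What the power above 90% refers to**

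Inputs from 5.5.2: 82 patients at each of 6 centres (492, so 246 per arm), effect 0.5 SD, two-sided 0.05. The intra-class correlation (ICC) is not stated, so 0.01 to 0.10 is assumed.

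- Ignoring clustering: 0.5/√(2/246) = 5.545, and power = Φ(5.545 − 1.960) = 99.98%.
- Stepped wedge with one centre per step, 7 periods, 82/7 patients per centre-period, total variance 1 and a random centre effect. The variance of the effect is the last diagonal element of (Σ Zᵢ′V⁻¹Zᵢ)⁻¹, and power = Φ(0.5/SE − 1.960).
  - Without period terms: 99.9% or more.
  - With period terms: SE 0.134, 0.146 and 0.147 at ICC 0.01, 0.05 and 0.10, giving 96.2%, 92.8% and 92.7%.

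The stated figure is therefore consistent with a mean-score comparison. It can be matched only as an inequality, because the ICC and the spread of the beta distribution are not given.

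**3. The same shift expressed as response**

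The protocol gives no response rates. Assume control response p₁ of 20-50% and a 0.5 SD shift on a normal latent scale, so p₂ = Φ(Φ⁻¹(p₁) + 0.5). The patient-level SD is √(p̄(1 − p̄)), where p̄ is the mean of p₁ and p₂, and the SE in step 2 scales by it. Example: p₁ = 30%, p₂ = 49.0%, SD 0.489, ICC 0.05. SE = 0.489 × 0.146 = 0.0714, and power = Φ(0.190/0.0714 − 1.960) ≈ 76%.

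| Control → intervention response | Power, 6 × 82, ICC 0.01 / 0.05 / 0.10 | Power, 8 × 82, same ICCs |
|---|---|---|
| 20% → 36.6% | 78.6 / 71.5 / 71.2% | 90.0 / 84.2 / 83.8% |
| 30% → 49.0% | 82.7 / 76.0 / 75.7% | 92.8 / 87.7 / 87.4% |
| 40% → 59.7% | 83.8 / 77.2 / 76.9% | 93.4 / 88.6 / 88.3% |
| 50% → 69.1% | 82.9 / 76.2 / 75.9% | 92.9 / 87.9 / 87.6% |

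**4. Mean change and response are different quantities**

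Illustration with assumed inputs: screening scores 5 to 10 in proportions 25, 20, 20, 20, 10 and 5%; SD of change 2.2; control mean drop 1.0 before rounding and truncation to 0-10. One treatment effect is spread evenly over patients (mean drop 2.1). The other gives an extra 4.8 points to a quarter of them. After rounding and truncation both have a mean drop of 2.09, but 50.9% and 47.8% respond, against 32.1% in control. The response differences are 50.9 − 32.1 = 18.8 and 47.8 − 32.1 = 15.7 points for the same mean effect.

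**5. What if the linear model is fitted to the 0/1 response?**

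A stepped-wedge simulation (6 × 82, 300 replicates, fixed centre and period effects standing in for the mixed model) gave a mean linear estimate of 0.188 against a true risk difference of 0.189. Type I error was 5.0% (logistic 4.3%) and power 67% (logistic 69%). With a Monte Carlo error of √(0.05 × 0.95/300) = 1.3 points on the type I error, the two models cannot be told apart there. This reading is workable, but the protocol does not state it.

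**The case against.** The strongest reply is that the outcomes of interest in 5.5.1 naturally include the primary one, so the linear model would be fitted to the 0/1 response. It would then estimate a risk difference, which is what the objective and the cost per responder need, and step 5 shows it can do so well. This stands to the extent that a reader who infers that the plan cannot estimate its primary objective goes too far. But the protocol does not declare this use. Its reported simulations concern NRS scores, and 5.5.2 and 5.2.3.1 point to a mean score.

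A statistical analysis plan may supply the model. That excuses missing detail. It does not excuse the protocol naming one model for everything with a justification that does not reach the primary endpoint.

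A reader might also infer that the plan wrongly omits the screening score as a covariate. The documents do not support that. Covariates are given as examples only, for "instance patient age, gender, ethnicity and other factors related to their type of disease; and" centre characteristics, and nothing excludes the screening score. It is true that on an integer scale 30% requires a drop of 2 points from a score of 5 or 6 and 3 points from 7 to 10. But the rationale in 5.2.1 chose a percentage rule knowing that the needed change varies with baseline, and response is already defined relative to the screening score. Different response rates by baseline within one arm are not bias. Bias would need a shift in case mix between phases, and nothing in the documents quantifies one. Since 5.2.3.1 hopes to lower scores across all screenings, the screening score may itself be affected by the intervention, so adjusting for it needs thought.

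**Conclusion.** The point holds as a mismatch between the primary outcome and the only main analysis stated. The model is linear and justified for 0-10 scores, while the endpoint is binary. On the reading that 5.5.2 and 5.2.3.1 support, the main analysis would estimate a secondary outcome. On the other reading it would estimate a risk difference, but by an undeclared route.

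The size is in what the power claim covers. The figure above 90% describes a mean-score comparison in patients scoring 2 or more. For response, the same shift gives 71-84% at 6 × 82 and 84-93% at 8 × 82. These figures assume control response of 20-50%, ICC 0.01-0.10, a normal latent shift, period effects in the model and one centre per step. A reader might infer that the trial is underpowered. That does not follow, because the protocol states neither response rates nor an ICC, and eight sites are planned. What follows is that power for the primary endpoint has not been stated.

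**What to change.** - In 5.5.1 and the trial summary, state that the primary analysis models responder yes/no, in patients screened at 5 or more, with a mixed-effects logistic model (glmer in the lme4 library already named). Include intervention and period terms and a random centre effect, and report the odds ratio and the model-based risk difference. The risk difference also feeds the cost per additional responder in 5.5.3.
- Keep linear mixed models for the NRS, quality-of-life and heiQ scores.
- In 5.5.2, state that the power above 90% refers to a mean-score comparison in patients scoring 2 or more, not to response in patients scoring 5 or more.
- In 5.2.3.1, item 2, reconcile the 0.5 SD reference to the primary outcome with the 30% definition in 5.2.1.
- Optional: adjust for the screening worst-pain score as a sensitivity analysis. This would be an addition, not the correction of an error.

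The cost is wording only. The software is the same, and the variables needed are already collected.

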## **Sample size**

100 patients with score 5+ on a numerical rating scale for pain at screening recruited at Week 1 for worst pain score (50 during the control arm and 50 during the intervention arm) per site, across eight sites.

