#### 3.2.1 Patients

##### 3.2.1.1. Inclusion criteria for patients contributing to primary outcome

- 1) Attend a participating oncology and palliative care centre as an outpatient during the study period
- 2) Have a diagnosis of current active cancer
- 3) Be able to self-complete a 0-10 numerical rating scale (NRS) for severity of worst and average pain in English, Chinese, Italian, Greek, Vietnamese or Arabic)
- 4) Choose not to opt-out of being contacted 1 week later to complete the NRS and give verbal consent to do so.
- 5) Score  $\geq 5$  on the NRS for worst pain

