#### 3.2.2 Unpaid carers

- 1) Be identified by a patient who has given verbal informed consent to participate in the study as providing them with substantial emotional and practical support in an unpaid capacity;
- 2) Provide verbal informed consent;
- 3) Have spoken and written English proficiency sufficient to complete the Carer Experience Scale (CES) (3) and/or interview.

603 **3.2.3 Centre staff**

- 604 1) Be employed on a permanent basis either full- or part-time at a participating cancer or  
605 palliative care centre in a role that provides clinical care to patients with cancer pain or  
606 front desk administrative support;  
607 2) Provide written informed consent.

608 **3.3 *Exclusion criteria***

609 **3.3.1 Patients**

- 610 • Participation at another centre taking part in the trial or at the same centre at a time when it  
611 was in the opposing arm;  
612 • Documented as having cognitive impairment that would preclude capacity to give informed  
613 consent.

614 **3.3.2 Unpaid carers**

- 615 • Patient for whom they provide care is not participating in any secondary outcome  
616 components.

617 **3.3.3 Centre staff**

- 618 • Working at a participating centre on a casual or agency basis.  
619

620 **INVESTIGATIONAL PLAN**

621 **3.4 Study design**

622 A stepped-wedge cluster randomised controlled trial with oncology and palliative care centres as  
623 units of randomisation will be undertaken to evaluate implementation of the cancer pain guidelines.

624  
625 In this design, randomisation concerns the sequence in which the intervention begins at each centre  
626 rather than whether it occurs at all (see Figure 1).

627  
628  
629

| Centres |         | Phases                  |                |  |
|---------|---------|-------------------------|----------------|--|
| 1       | Control | Training & Intervention | Sustainability |  |
| 2       | Control | Training & Intervention | Sustainability |  |
| 3       | Control | Training & Intervention | Sustainability |  |
| 4       | Control | Training & Intervention | Sustainability |  |
| 5       | Control | Training & Intervention | Sustainability |  |
| 6       | Control | Training & Intervention | Sustainability |  |
| 7       | Control | Training & Intervention | Sustainability |  |
| 8       | Control | Training & Intervention | Sustainability |  |

630

631 **3.4.1 Figure 1. Stepped wedge design with staggered introduction of**  
632 **training/intervention in 8 centres**

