633

634 **3.5 Rationale for study design**

635 While needing a slightly longer timeline than a parallel design, a stepped-wedge cluster randomised  
636 controlled trial has the following translational research advantages:

637

- 638 1) all centres will receive the intervention so have an added incentive to participate;  
639 2) the design controls for between-centre variation in baseline practice;  
640 3) statistical power is boosted by the opportunity to assess intervention effects in a pre/post  
641 comparison across centres;  
642 4) at any given time beyond the baseline period, the design allows a randomised comparison of  
643 intervention and control centres; and  
644 5) assessment of longitudinal effects (e.g. sustainability) can occur (42).

645

646 A stepped-wedge cluster randomised controlled trial design also allows greater diversity of centres  
647 to be included to allow broad applicability of the results, without compromising comparability or  
648 requiring matching of sites. Recruitment during the control arm at each centre will commence at  
649 least 3 months prior to training to enable sufficient time for the smaller centres to recruit the target  
650 sample.

651  
652 Outcome data collection for patients in the control arm will be censored prior to their centre making  
653 the transition to the intervention arm. For a period of 4 weeks after the training phase, data will not  
654 contribute to outcome measurement, to allow time for the intervention to become consolidated as  
655 routine practice.

656  
657 Importantly, patients can participate in only one of the arms, not both. This means that patients who  
658 participate at their centre during the control arm will be ineligible to participate in the intervention  
659 arm.

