### 660 **3.6 Randomisation**

661 Randomisation will be concerned with the time at which each centre transitions from the control  
662 arm to training and intervention. Stratification will be unnecessary because each centre will serve as  
663 its own control. Patients will be automatically allocated to usual care or intervention arms  
664 according to the current arm of their treatment centre upon their first presentation. Participants will  
665 be sequentially allocated an ID number, which will be used for all subsequent study documentation  
666 for that participant.

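### The repeat analysis for prior care is restricted to new referrals in the intervention arm only, so as written the arms differ in referral status

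*Protocol*

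**What the plan says.** Section 5.5.1 of the protocol plans two versions of each analysis. It says "Analyses will be repeated for all patients" "and patients newly referred during the intervention arm to control for the possibility that outcomes" "are influenced by care received prior to the intervention being implemented". So the first set is all patients, and the second is patients newly referred during the intervention arm. No set of patients newly referred during the control arm is named in that section or elsewhere in the protocol.

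The eligibility criteria do not separate new from established patients in either arm. Section 3.2.1.1 admits those who "Attend a participating oncology and palliative care centre as an outpatient during the study period". The exclusion in section 3.3.1 that concerns the opposing arm is about taking part in the trial, not about earlier care: "Participation at another centre taking part in the trial or at the same centre at a time when it" was in the other arm.

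Section 3.6 allocates patients "according to the current arm of their treatment centre upon their first presentation". It does not say whether this means the first attendance at the centre or the screen at which the patient enters the study.

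**The concern.** An analysis set that answers a question about prior care has to be formed in the same way in both arms. Here the only stated criterion refers to the intervention arm. Established patients drop out of that arm and, on the literal reading, stay in the control arm. Referral status then goes with the arm in this analysis. If new and established patients differ in how often they reach a 30% fall within a week, part or all of the observed difference could come from who is in each group.

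The restriction does serve its stated purpose on the intervention side, because it removes patients whose care straddled the change in practice. What is at stake is how the result is read. Agreement between the restricted and the full analysis could be taken as reassurance, and disagreement as evidence of carry-over, when either could reflect referral mix.

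The wording of section 3.6 adds a second uncertainty, because one reading of it would leave the restricted set no different from the full one.

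**Working it through.** **The plan's own figure.** The sentence in question gives no number. The nearest stated figure is power above 90% in section 5.5.2, for a 0.5 SD effect, two-sided 0.05, with 82 patients at each of 6 centres. 82 × 6 = 492, or 246 per arm. A simple two-mean calculation gives 0.9998, which agrees with the claim. It serves here only to supply a sample size; the point does not depend on it.

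**Inputs.** From the protocol: 246 per arm and two-sided 0.05. Assumed, because the protocol gives none of them:
- share q of new referrals: 25%, 50% or 75%, the same in both arms before restriction;
- response rate in established patients: 30%;
- gap d (new minus established): 5, 10 or 20 points;
- no true intervention effect.

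**Formulae.**
- Control response, unrestricted: q × (30 + d) + (1 − q) × 30 = 30 + q × d.
- Intervention response, new referrals only: 30 + d.
- Spurious difference: (30 + d) − (30 + q × d) = (1 − q) × d.

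The bias depends on q in the control arm only, and the 30% cancels.

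**Example with d = 10.** At q = 25% the control rate is 32.5% against 40%, a difference of 7.5 points. At q = 50% it is 35% against 40%, or 5 points. At q = 75% it is 37.5% against 40%, or 2.5 points.

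**Bias in points, with the resulting type I error in brackets** (two-proportion comparison, 246 controls, 246 × q intervention patients, clustering and period effects ignored):

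| q | d = 5 | d = 10 | d = 20 |
|---|---|---|---|
| 25% | 3.75 (0.09) | 7.5 (0.20) | 15 (0.58) |
| 50% | 2.5 (0.08) | 5 (0.16) | 10 (0.45) |
| 75% | 1.25 (0.06) | 2.5 (0.08) | 5 (0.18) |

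If d = 0 the bias is zero. If d is negative, the bias has the same form with the opposite sign.

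**Comparison with the alternatives.** With the same q in both arms, the all-patients analysis has no bias from referral status: (30 + q × d) − (30 + q × d) = 0. Restricting both arms also gives zero, (30 + d) − (30 + d), and does so for every q and d, even if q differs between arms.

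**What the two-sided restriction costs.** It leaves 246 × q per arm: about 62, 123 and 184 at q = 25%, 50% and 75%. Power for a 0.5 SD difference in means is then 79%, 97.5% and 99.8%, again ignoring period effects. These figures are for a continuous score, not for the responder outcome.

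**Sections 3.6 and 5.5.1 side by side.** If first presentation means first attendance at the centre, every intervention patient is already a new referral. The restricted set then equals the intervention arm and the repeat analysis is redundant. If it means the qualifying study screen, established patients can enter the intervention arm and the repeat analysis has something to do. Only the second reading gives section 5.5.1 a purpose, but section 3.6 does not say so.

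**The case against.** **Silence is not asymmetry.** The sentence does not say that controls stay unrestricted. A symmetric intent is possible, and the analysis plan, not at hand, may spell it out. This stands as a caution. But the protocol itself fixes the set by referral in the intervention arm, and a plan that follows it literally inherits the problem.

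**The restriction does what it claims.** Only intervention patients can have had usual care first and the intervention afterwards, and the restriction removes that carry-over. This stands. To say that the check introduces the very confounding it is meant to remove would go too far: it deals with earlier care in one arm and opens a separate difference in referral status.

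Four stronger readings are tempting, and the protocol does not support them.

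- A reader might infer from section 3.6 that an established patient who first screens positive after crossover is counted as a control while receiving the intervention, diluting the effect. Section 3.5 stops control-arm outcome collection before a centre crosses over, so no such exposed control outcome would be collected. That reading also could not hold together with the bias worked out above, which needs established patients in the intervention arm.
- A reader might take this to be the only planned safeguard. It is not. Section 3.5 also confines each patient to one arm and sets aside four weeks of data after training. Section 5.5.1 allows patient covariates, and section 5.2.5 lists time since diagnosis and current treatment among the descriptive and control variables.
- A reader might suppose that the bias favours the intervention. The protocol gives no response rates by referral status, and new referrals could respond better or worse.
- A reader might argue that the main comparison is already unbalanced, because patients who "participate at their centre during the control arm will be ineligible to participate in the intervention" arm, so that control recruitment uses up the established pool first. Only actual participants are barred, the target is "50 during the control arm and 50 during the intervention arm) per site, across eight sites", and no pool size or referral share is given. It is a possibility that the protocol can neither confirm nor exclude.

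**Conclusion.** The point holds, in a limited form. As written, the repeat analysis in section 5.5.1 compares newly referred intervention patients with a control group of mixed referral status. Its bias from that source is (1 − share of new referrals in control) × (response gap): 2.5 to 7.5 points in absolute size for an assumed 10-point gap and assumed shares of 75% to 25%. The protocol supplies neither the share nor the gap, so the size is illustrative and the sign unknown.

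The flaw lies in a supporting analysis; this restriction leaves the main analysis unchanged. The sentence should nevertheless be corrected, because a sensitivity analysis with its own case-mix difference cannot cleanly support or question the main result. The phrase in section 3.6 should be defined at the same time, since on one reading the repeat analysis would be redundant.

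**What to change.** 1. In section 5.5.1, define the restricted set as patients newly referred during the phase in which they were screened, in both the control and the intervention arm. Analyse it with the same model as the main analysis.
2. Record new or established status at the index screen in both phases, with a stated definition of new referral. Neither Table 1 nor the descriptive variables in section 5.2.5 list a referral date or this status.
3. In section 3.6, state that first presentation means the qualifying study screen, so that it agrees with section 5.5.1.

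The cost is two reworded sentences and one extra item from clinic records for control patients. The symmetric subset is smaller and its interval wider. If only a quarter of patients were new referrals, power for a 0.5 SD difference would fall to about 79% on the simple calculation above. It should therefore be reported as an estimate with its interval, not judged by whether it reaches significance.
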